### Hypothesis

Our hypothesis is that SNRBs have a lower recurrence rate than CESIs in treating patients with single-level LSS.

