**Fig. 1 Fig1:**
[figure not shown]
Schematic presentation of patient flow. LSS, lumbar spinal stenosis; CESI, caudal epidural steroid injection; SNRB, selective nerve root block; NRS, numeric rating scale; ODI, Oswestry Disability Index; LANSS, Leeds assessment of neuropathic symptoms and signs

The main outcome measures include the Leeds Assessment of Neuropathic Symptoms and Signs (LANSS) pain scale to determine whether the pain experienced is due to nerve damage, the Oswestry Disability Index (ODI) to assess functional status, and a numeric rating scale (NRS) for pain to evaluate pain intensity [20]. Two days before the procedure, we will assess the condition of patients using the LANSS pain scale, ODI, and NRS for pain. One day, 2 weeks, 3 months, 6 months, and 1 year after the procedure, we will evaluate these patients again using the NRS for pain and the ODI.

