### Data collection

We will evaluate the treatment outcomes using the NRS and ODI 1 day, 2 weeks, 3 months, 6 months, and 1 year after the procedure. The treatment plan and evaluation of results are shown in Table 3.

**Table 3 Tab3:** Treatment plan and evaluation of results

Data collection/recording	Person in charge	Observational phase		Follow-up phase			
		2 days before intervention	1 day after intervention	2 weeks after intervention	3 months after intervention	6 months after intervention	1 year after intervention
Obtaining informed consent	[name]	×					
Collecting patients’ basic information and medical history	[name]	×					
Screen patients for eligibility	[name]	×					
LANSS pain scale	[name]	×					
ODI	[name] [name]	×	×	×	×	×	×
NRS for pain	[name] [name]	×	×	×	×	×	×

*LANSS*, Leeds Assessment of Neuropathic Symptoms and Signs Pain Scale; *ODI*, Oswestry Disability Index; *NRS*, numeric rating scale

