### Outcome measures

Multiple outcome measures were utilized which included the NRS (0–10 scale) pain scale and the ODI on a 0–50 scale, with assessment at 1 day, 2 weeks, 3 months, 6 months, and 1 year after the procedure. The Oswestry Disability Index (ODI): back pain-related dysfunction will be assessed using the ODI. The ODI contains 10 questions about daily activities, including inventories of pain intensity, personal care, lifting, walking, sitting, standing, sleeping, sexual life, social life, and traveling. Each question is rated on a scale from 0 to 5 points; the lower the score, the less disabled the person is by the pain. The NRS represented no pain with a 0 and the worst pain imaginable with a 10. NRS is an instrument for the self-assessment of pain and comprises a scale with 0 and 10 at either end of a straight line. The participants marked a point on the line to indicate their level of average pain. The value and validity of the NRS and ODI have been reported [28, 29]. The main outcome measures of the present study were ODI and NRS scores after follow-up and the final recurrence rate calculated according to the requirements. ODI and NRS scores were obtained by designated personnel after follow-up work. After obtaining the above two scoring data, the curative effect was evaluated according to the requirements of Table 4, and the recurrence rate was obtained. According to the ultimate purpose of this study, the recurrence rate plays a very important role in the outcome indicators. ODI and NRS also provide the basis for the final calculation of recurrence rate, which significantly affects the evaluation of the efficacy of each subject, and also plays a decisive role in the research results. Specific criteria for evaluating the efficacy are shown in Table 4.

**Table 4 Tab4:** Efficacy evaluation

Cured: neither CESI nor SNRB cured LSS	
Marked effect: NRS score < 2 points or ODI score < 50%	
Effective: NRS score 2–4 points or ODI score 50–70%	
Relapse: NRS score > 4 points or ODI score > 70% or the use of analgesics of the patient’s own choice	

*Note*: We will record the time a patient has recurrence and stop follow-up

*CESI*, caudal epidural steroid injection; *SNRB*, selective nerve root block; *LSS*, lumbar spinal stenosis; *NRS*, numeric rating scale; *ODI*, Oswestry Disability Index

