## Discussion

Both SNRBs and CESIs have proven efficacy against LSS. However, there are no studies comparing the effectiveness of these two treatments in LSS. In clinical practice, primary care physicians often have to choose between these two procedures based on their own experience as there is no guideline for them to refer to. Such subjectivity raises the risk of adopting a suboptimal treatment plan for a patient, which can result in less than desirable outcomes and increase the uncertainty surrounding the prognosis of patients. In severe cases, treatment can fail, increasing patients’ pain and economic burden. To avoid patients receiving inappropriate treatment, we evaluated the effects of SNRB and CESI treatment for LSS. We will divide recruited LSS patients into two groups and offer them either SNRBs or CESIs. Data including duration of symptom relief and time to relapse in patients in the two groups will be recorded, and the recurrence rate will be calculated to determine whether SNRBs or CESIs are more effective in relieving patients’ symptoms long term. We hope our findings will provide a reference for physicians and help them make a choice between SNRBs and CESIs for LSS patients based on scientific and clinical evidence so that these patients can receive optimal treatment with maximal efficacy.

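### Follow-up stops at relapse, so NRS and ODI scores after the relapse visit are never collected, although both are main outcomes to 1 year

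*Protocol article*

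**What the plan says.** - **Main outcomes** (Outcome measures): "The main outcome measures of the present study were ODI and NRS scores after follow-up and the final recurrence rate calculated according to the requirements".
- **Schedule** (Data collection section): "We will evaluate the treatment outcomes using the NRS and ODI 1 day, 2 weeks, 3 months, 6 months, and 1 year after the procedure". Table 3 marks NRS and ODI at each of these visits with no exception for relapsed patients. The Methods/design text below Fig. 1 repeats the schedule: "we will evaluate these patients again using the NRS for pain and the ODI".
- **Relapse** (Table 4): "Relapse: NRS score > 4 points or ODI score > 70% or the use of analgesics of the patient’s own choice".
- **Stopping rule** (note to Table 4): "We will record the time a patient has recurrence and stop follow-up".
- **Hypothesis**: "SNRBs have a lower recurrence rate than CESIs in treating patients with single-level LSS". The Discussion adds: "Data including duration of symptom relief and time to relapse in patients in the two groups will be recorded".

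The article does not provide for scoring after relapse. Its section on dropouts and loss to follow-up deals with patients who withdraw or are removed by the chief investigator, and does not name relapsed patients.

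**The concern.** The event that ends follow-up is defined by the scores that follow-up is meant to measure. After the first NRS above 4 or ODI above 70%, or after analgesic use, nothing further is due from that patient. Those who remain at 3 months, 6 months and 1 year have been selected for low scores at every earlier visit. The hypothesis expects more relapse with CESI, so the CESI arm would lose more of its worst patients.

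A comparison of late means among the remaining patients is then no longer a comparison of the randomised groups. At stake are the late NRS and ODI results, two of the three main outcomes. The gap cannot be closed afterwards: an analysis plan can choose how to treat missing scores, but it cannot supply scores that were not collected.

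**Working it through.** The plan gives no figure for the effect of this rule, so there is none to reproduce.

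**Inputs from the protocol article.** Relapse cut-off NRS > 4 (Table 4); five post-procedure visits (Table 3); SD 2.17 and expected NRS of 0–1 with SNRB and 3–4 with CESI (Sample size).

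**Assumptions.** The ranges 0–1 and 3–4 are read as NRS levels at follow-up, with midpoints 0.5 and 3.5. Scores are normal, and in the simulations correlated within patient and clipped to 0–10. Only the NRS trigger is modelled. Scores after relapse are taken to continue on the same course.

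**Step 1: which scores are lost.** A relapse found at a visit leaves that visit's score on record. Every later visit is lost, so loss can begin at the 2-week visit if relapse is found on day 1.

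**Step 2: one visit, by hand (no clipping).** The share relapsing is 1 − Φ(z), with z = (4 − mean)/SD.
- CESI: z = (4 − 3.5)/2.17 = 0.230, share 41%.
- SNRB: z = (4 − 0.5)/2.17 = 1.613, share 5%.

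The mean of those not relapsing is mean − SD × φ(z)/Φ(z).
- CESI: 3.5 − 2.17 × 0.3885/0.5911 = 2.07.
- SNRB: 0.5 − 2.17 × 0.1086/0.9466 = 0.25.

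The difference among patients not in relapse is 2.07 − 0.25 = 1.82, against 3.5 − 0.5 = 3.0 among all patients.

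**Step 3: five visits, by simulation.** SD 2.17, correlation 0.4–0.8, follow-up stopped at the first NRS > 4, score at the relapse visit kept.

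| True 1-year difference | Among patients still followed | Share of the difference lost |
|---|---|---|
| about 1.1 | 0.4–0.8 | (1.1 − 0.8)/1.1 = 27% to (1.1 − 0.4)/1.1 = 64% |
| about 2.4 (means 3.5 v 0.5) | 1.05–1.4 | (2.4 − 1.4)/2.4 = 42% to (2.4 − 1.05)/2.4 = 56% |

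A wider set of scenarios (correlation 0.3–0.8, SD 1.5 or 2.17, with and without worsening over time) gave an observed difference of about 23–83% of the true one at 3 months to 1 year. That range includes analyses that drop the relapse-visit score. With means 3.5 v 0.5 and SD 2.17, about 12–40% of CESI and 71–89% of SNRB patients were still scored at 1 year. The loss in size is smaller when the arms separate late, because fewer patients have then been removed selectively.

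**Step 4: other analyses of the same truncated data.**

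| True difference | Likelihood model | Last score carried forward |
|---|---|---|
| about 1.1 | 1.06–1.26 | 0.83–1.23 |
| about 2.4 | 2.43–2.47 | 2.65–3.06 |

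**Step 5: equal arms.** The simulated difference was zero with and without the stopping rule.

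**The case against.** - **The direction is not fixed.** A reader might infer that the rule always biases towards no difference. Step 4 shows otherwise: the same data can give attenuation, near-recovery or exaggeration. The Statistical methods section names no test or missing-data method for NRS or ODI, and an analysis plan may exist. This stands, so the direction is conditional. But the likelihood result depends on its model being right, and on relapse being explained by recorded scores. Relapse through analgesic use between visits is not so explained.
- **Relapsed patients do have scores.** It is tempting to say that late scores exist only for patients who have not relapsed. That is inexact, because a relapse found at a visit has that visit's score. Keeping it does not remove the shrinkage (Step 3).
- **The long-term question survives.** The hypothesis and stated aim concern recurrence, and the Discussion uses the recurrence rate to judge long-term relief. Recurrence is recorded before follow-up stops. This stands: the harm is confined to late NRS and ODI.
- **Adverse events.** A reader might infer that safety observation also ends at relapse. The note sits under the efficacy criteria, and the safety section describes evaluation during the study period. The documents do not say that it stops. Observation would be shortened only if the note is read to cover it.
- **The schedule may be only a plan.** A visit table can coexist with a rule that ends follow-up at an event. That is arguable, but not for scores named as main outcomes to 1 year with no exception stated.
- **The size is model-based.** The 1.1-point effect is assumed, and the ODI and analgesic triggers are left out. This also stands.

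**Conclusion.** The concern holds in a limited form. As written, NRS and ODI are not collected at visits after the relapse visit. The loss depends on the outcome and is larger in the arm that relapses more. If the arms differ as hypothesised and the scores of patients still followed are compared, the late difference is too small: about 0.4–0.8 for a true NRS difference of about 1.1, under the assumptions listed. These figures are for NRS; the same mechanism applies to ODI, for which no size was computed.

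The documents do not support a claim of unconditional bias towards no difference, nor that the trial cannot answer its recurrence question, nor that adverse event observation is known to end at relapse. What remains is still important, because no later analysis can replace scores that were not collected.

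**What to change.** Reconcile the Table 4 note with Table 3 by replacing the note with:

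> The date of recurrence is recorded; all randomised patients continue the scheduled NRS and ODI assessments (and adverse event recording) to 1 year, whether or not they have relapsed.

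Compare NRS and ODI in all randomised patients, and report analgesic use or other treatment after relapse by arm. For patients already stopped, collect the remaining questionnaires where they agree. The change concerns data collection only and alters no treatment.

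**Cost.** The visits are already in Table 3, so the main cost is wording. Recruitment began in April 2020 with completion expected by the end of 2021 (Trial status), so some stopped patients would need re-contact, and visits already missed cannot be recovered. Post-relapse scores may partly reflect other treatment, which is why that treatment should be reported beside them.

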For the control group and the experimental group, other treatments allowed for the patients are as follows: (1) both groups can be given routine nursing treatment in Department II of Spine of Traditional Chinese Medicine Hospital of Xinjiang Uygur Autonomous Region, including daily inquiry of patients’ condition, pain improvement, and care for patients. (2) Acupuncture and moxibustion treatment of lumbar spinal stenosis was performed by a doctor designated by the Acupuncture and Moxibustion Department of the said hospital. Standardized acupuncture and moxibustion treatment of lumbar spinal stenosis was adopted, that is, acupuncture and moxibustion treatment was the same for all subjects. (3) The massage treatment of lumbar spinal stenosis was performed by the designated physician in the Department of Massage of the said hospital. The standardized treatment of lumbar spinal stenosis with acupuncture and massage was used, that is, all subjects had the same massage treatment. (4) The treatment can be performed by the designated nurse of Department II of Spine and ensure that all subjects are electrically treated in the same position. The other treatments allowed are traditional Chinese medicine treatment, which can play the role of adjuvant treatment, and the two groups of patients received the same treatment. As a result, the effect of the above treatment on the experimental results can be avoided. For the control group and experimental group, the other treatments prohibited from the patients are as follows: (1) In the course of the experiment, other invasive treatments for lumbar spinal stenosis were performed, (2) It is forbidden for the subjects to take drugs that can improve the clinical symptoms of lumbar spinal stenosis. (3) Patients were not allowed to receive other treatments for lumbar spinal stenosis without the consent of the researcher. (4) They took related analgesics by themselves.

[name], a physician of Spine Department II, had an informed conversation with the subjects 2 days before the operation and obtained consent from the subjects. After [name] obtained the informed consent from the subjects, [name], a physician of Spine Department II, asked the subjects for the basic information and related medical history of the patients required for the experiment, which was also completed 2 days before the operation. [name], a physician of Spine Department II, checked whether the subjects met the prescribed criteria 1 day before the operation and finally determined whether they were included in the experiment. Researcher [name] completed his work of LANSS scoring 2 days before the operation after [name] and [name] completed their work. After then, [name] and [name] completed the follow-up collection of ODI and NRS. It should be noted that for the same subject, the same person should always follow up and collect data, which cannot be carried out alternately. The follow-up collection of data must be completed within 24 h on the specified date. [name] is responsible for sorting and inputting the collected data into the designated data collection table and setting the password to save independently. This work is completed within 24 h after receiving the data.

### Dropouts and loss to follow-up

All patients have the right to drop out of the study at any time. If a patient chooses to discontinue participation, we will withdraw consent from this patient and terminate the study. The chief investigator can also terminate a subject’s participation if he/she breaks the rules governing this study or has severe adverse events. Data on these subjects will be excluded from our final analysis.

### Statistical methods

Two investigators will use EpiData 3.0 for data entry. SPSS18.0 will be used to analyze all data. All patients’ demographic and clinical characteristics (e.g., gender, age, and weight) will be subject to descriptive analysis. Quantitative data will be expressed as mean ± standard deviation, medians, and ranges, while qualitative data will be expressed as frequency and percentage. A chi-squared test will be used to compare the incidence of adverse events between patients in the two groups.

### Publication of study results

The study results will be published in relevant medical journals. The chief investigator together with the members of the research management team and other investigators will write the manuscript and submit it to a journal for publication.

## Discussion

Both SNRBs and CESIs have proven efficacy against LSS. However, there are no studies comparing the effectiveness of these two treatments in LSS. In clinical practice, primary care physicians often have to choose between these two procedures based on their own experience as there is no guideline for them to refer to. Such subjectivity raises the risk of adopting a suboptimal treatment plan for a patient, which can result in less than desirable outcomes and increase the uncertainty surrounding the prognosis of patients. In severe cases, treatment can fail, increasing patients’ pain and economic burden. To avoid patients receiving inappropriate treatment, we evaluated the effects of SNRB and CESI treatment for LSS. We will divide recruited LSS patients into two groups and offer them either SNRBs or CESIs. Data including duration of symptom relief and time to relapse in patients in the two groups will be recorded, and the recurrence rate will be calculated to determine whether SNRBs or CESIs are more effective in relieving patients’ symptoms long term. We hope our findings will provide a reference for physicians and help them make a choice between SNRBs and CESIs for LSS patients based on scientific and clinical evidence so that these patients can receive optimal treatment with maximal efficacy.

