## Abstract

**Background:**

Lumbar spinal stenosis (LSS) is a common degenerative condition associated with old age. Its incidence continues to increase with the rapidly aging population in China. Treatment for LSS usually begins with conservative treatments, as some patients refuse surgical procedures or have surgery contraindications. Caudal epidural steroid injections (CESIs) and selective nerve root blocks (SNRBs) are two commonly used conservative treatments for LSS, which have proven to be effective at relieving LSS symptoms in many studies. However, there are no randomized controlled trials comparing these two procedures. We planned the first study to assess which one of these two procedures is more effective in treating LSS. We will compare the efficacy of these two treatment methods in terms of duration of symptom relief and recurrence rate. We hope our findings will help clinicians choose an optimal treatment for LSS patients.

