Most patients seeking treatment for lower back pain have LSS. Treatments for LSS can be conservative and surgical. Conservative management is successful in most patients and is recommended as first-line treatment. Common conservative treatments for LSS include caudal epidural steroid injections (CESIs) and selective nerve root blocks (SNRBs). The reasons for their popularity among primary care physicians are as follows: First, compared with conventional surgical interventions, SNRBs and CESIs greatly reduce the time that physicians are exposed to X-rays, thus protecting their health. Second, SNRBs and CESIs are easy to perform and have a short learning curve.

The efficacy of CESIs has been demonstrated in many studies. Delport et al. analyzed 140 patients treated with epidural steroid injection (ESI) [11]. Fifty-three percent reported improvement in their functional abilities and 74% were at least somewhat satisfied with ESI as a form of treatment. Fukusaki et al. conducted a prospective, randomized, double-masked trial evaluating the efficacy of ESI in 53 patients with LSS [12]. The patients were randomized into three groups: epidural saline injection, epidural local anesthetic, and epidural anesthetic plus steroid. They found that there was a significant difference in the efficacy of the different treatments at 1 month. However, after 3 months, there was no significant difference between the three groups, proving the short-term effect of ESI. Koc et al. reported findings from a prospective, randomized controlled trial of 33 patients comparing the effects of ESI and a conservative inpatient physical therapy program on pain and function for patients with LSS [13]. They found that the ESI group had significant improvement in visual analog scale (VAS) scores at the 2-week follow-up. They concluded that ESI and physical therapy are equally effective in treating LSS up to 6 months of follow-up, while ESI has better short-term efficacy.

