To our knowledge, however, there have been no randomized controlled trials comparing the efficacy of SNRBs and CESIs. In clinical practice, primary care physicians often have to choose between a selective nerve block and a caudal epidural injection based on their own experience, as there is no guideline for them to refer to. To fill this gap, we plan to conduct the first study to compare the effects of SNRBs and CESIs on LSS. We will use outcome measures such as duration of symptom relief and recurrence rate to determine whether SNRBs or CESIs are more effective. We hope our findings will help physicians make a choice between SNRBs and CESIs for LSS patients.

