## Methods/design

This is a randomized controlled trial, aimed at comparing the recurrence rate of LSS following treatment with SNRBs and CESIs in patients with one-level LSS. This study was approved by the Ethics Committee of the Fourth School of Clinical Medicine of Xinjiang Medical University and will be conducted in accordance with the World Medical Association Declaration of Helsinki. This study is registered in the Chinese Clinical Trial Registry (Registration No. ChiCTR1900028038). Written informed consent will be obtained from all patients before initiating treatment.

Evaluation of the results and statistical analysis will be performed by professionals who are blinded to the group assignment. Participant flow is shown in Fig. 1. The study will last for 1 year. Patients will be randomly divided into two groups with patients in group A receiving a CESI and patients in group B receiving an SNRB.

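### Duration of relief is an aim and time of relapse is recorded, but the main outcomes and the deciding step use only the final recurrence rate, which ignores timing and partial follow-up

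*Protocol article*

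**What the plan says.** Duration is part of the question. The Abstract states: "We will compare the efficacy of these two treatment methods in terms of duration of symptom relief and recurrence rate". The Background repeats this, naming "outcome measures such as duration of symptom relief and recurrence rate to determine whether SNRBs or CESIs are more effective".

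The timing is collected. The note to Table 4 (Outcome measures) reads: "We will record the time a patient has recurrence and stop follow-up". The Discussion also says that duration of relief and time to relapse are recorded.

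The comparison itself is framed on the rate:
- The Hypothesis is that "SNRBs have a lower recurrence rate than CESIs in treating patients with single-level LSS".
- The Methods describe a trial "aimed at comparing the recurrence rate of LSS following treatment with SNRBs and CESIs in patients with one-level LSS".
- Outcome measures lists ODI, NRS and the final recurrence rate as the main outcomes. Neither time to relapse nor duration of relief is on that list.
- The Discussion closes the chain: "the recurrence rate will be calculated to determine whether SNRBs or CESIs are more effective", with reference to long-term relief.

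Three other statements bear on the point. The Sample size section allows for 20% loss to follow-up. Dropouts and loss to follow-up excludes the data of subjects who withdraw or whose participation is terminated. Statistical methods summarises qualitative data as frequencies and percentages.

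**The concern.** An aim stated in the Abstract and the Background, with its data on file, does not appear among the main outcomes or in the deciding step. Table 4 makes relapse a yes/no category, so a final recurrence rate built from it most naturally reads as a proportion by 1 year. Such a proportion loses two things:

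- **Order of relapses.** Two procedures with clearly different durations of relief can show the same rate. The trial could then report no difference on a question that it set out to answer.
- **Partial follow-up.** A patient seen relapse-free at 6 months and then lost has no 1-year status. Under the exclusion rule a withdrawn patient contributes nothing, although half a year without relapse was observed. Because follow-up stops at relapse, patients who relapse early are complete, while those still relapse-free remain exposed to loss. Excluding the lost patients therefore tends to push the crude rate upwards.

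**Working it through.** **Inputs.** From the protocol: visits at 1 day, 2 weeks, 3, 6 and 12 months; 76 patients, so 38 per group; 31 per group before the allowance for loss; 20% loss. The protocol gives no relapse rates, so there is no figure of its own to reproduce here, and every relapse pattern below is an assumption. Tests are two-sided at 5%.

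**1. Same rate, different duration (31 per group).** Let 20 patients relapse in each group, so the rate is 20/31 = 64.5% in both and the difference is 0. Date relapses to visits and count patients without relapse as 12 months.
- Group with 10 relapses at 2 weeks (0.46 months) and 10 at 3 months: (10 × 0.46 + 10 × 3 + 11 × 12)/31 = 5.4 months relapse-free on average.
- Group with 10 at 6 months and 10 at 12 months: (10 × 6 + 10 × 12 + 11 × 12)/31 = 10.1 months.

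The rate does not register a gap of 4.7 months. A log-rank test on these data gives p = 0.068, so the example shows lost information, not an assured significant result.

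**2. Partial follow-up (assumed counts, one group of 38).** Suppose 10 relapse by 6 months, 8 of the other 28 are lost after the 6-month visit, and 10 of the 20 seen at 1 year have relapsed.
- Crude rate with the lost patients excluded: (10 + 10)/30 = 66.7%.
- Life table: 1 − (28/38) × (10/20) = 63.2%.

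The life table uses all 38 patients, and the crude figure is 3.5 points higher.

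**3. Power by simulation (38 per group, relapse dated to the five visits).** The two-sample test of 1-year proportions is compared with the log-rank test on visit of relapse.

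| Assumed pattern | 1-year proportion | Log-rank | Difference (points) |
|---|---|---|---|
| Proportional hazards, 1-year relapse 40% vs 15% | 70% | 70% | 0 |
| Proportional hazards, 60% vs 30% | 76% | 78% | +2 |
| Proportional hazards, 80% vs 50% | 79% | 83% | +4 |
| Proportional hazards, 80% vs 60% | 50% | 54% | +4 |
| Delay: relapse-free A 95/80/45/30/20%, B 97/92/75/50/30% | 18% | 48% | +30 |
| Late separation: relapse-free A 95/88/75/55/30%, B 95/88/75/66/60% | 76% | 56% | −20 |

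With 20% of patients lost at a random visit (censored in the log-rank test, dropped from the proportion), the proportional-hazards gains are 2 to 6 points, and the delay pattern gives 47% against 16%. An independent repeat with 6,000 runs per pattern agreed to within about 3 points, with gains of about 0 to 5 points under loss.

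A further set with hazard ratio 0.5 and no loss shows where the proportional-hazards gain becomes larger. It is about 1 to 2 points when 50 to 70% of CESI patients relapse (44% vs 45%; 59% vs 61%). It is 8 to 13 points only when 90 to 95% do (66% vs 74%; 65% vs 78%).

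**The case against.** A reader might infer that the recurrence rate is the wrong deciding measure and that time to relapse should replace it. The protocol does not support this. The hypothesis and the Methods aim are both framed as recurrence rate, and the Discussion asks about long-term relief, for which status at 1 year is a coherent target. The late-separation row shows that a log-rank test can cost about 20 points of power even when the curves do not cross.

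Nor can it be said that the protocol expects the 1-year rates to converge. The Background remark that "after 3 months, there was no significant difference between the three groups, proving the short-term effect of ESI" reports one trial of epidural steroid against saline or anaesthetic, not CESI against SNRB. The Background also cites series with lasting relief after SNRB in 60% and 79% of patients, which would point to rates that diverge.

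It is also fair to say that the term rate is never defined as a crude proportion, so a Kaplan-Meier rate is compatible with the text. ODI and NRS are main outcomes as well, and duration is named as a comparison in the Abstract and Background. The choice of test may sit in an analysis plan that is not shown, and the absence of a named survival method is not the point here.

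What stands is the mismatch within the document. Duration is a stated basis for comparing the treatments and its data are recorded, but it is missing from the main outcomes and from the deciding step. In addition, the stated exclusions rule out the censoring that would use partial follow-up.

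**Conclusion.** The point holds as a gap between a stated aim and the measures chosen to answer it. It does not show that the recurrence rate is an invalid endpoint.

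That a 1-year count ignores timing follows from its construction and needs no assumption beyond reading the rate as a yes/no count. The size of the effect on power does rest on assumed relapse patterns:
- Proportional hazards: about 0 to 6 points gained by a visit-dated log-rank test with up to 80% relapse after CESI, and 8 to 13 only at 90 to 95%.
- Mainly delayed relapse: about 30 points gained.
- Late separation only: about 20 points lost.

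Because the sign can go either way, the two measures belong side by side. The change is worth making because it is cheap and answers the duration question, not because a power gain is assured.

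**What to change.** 1. Keep the 1-year recurrence rate as the deciding measure, in line with the Hypothesis and the Methods aim. Define it as the Kaplan-Meier or life-table estimate at 1 year on the five visits, per group, with the difference and 95% CI. Include all randomised patients and censor at the last visit attended without relapse.
2. Amend Dropouts and loss to follow-up to match, so that data gathered before withdrawal or termination are retained.
3. Add time to first relapse, grouped by scheduled visit, to the outcomes as a named comparison of duration of relief. Use a grouped log-rank test or a discrete-time complementary log-log model with visit as a factor. State that it stands alongside the rate and is not the sole deciding test.
4. Report the relapse-free proportion at each visit, which shows delay, late separation or crossing.

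**Cost.** Wording in Outcome measures, Statistical methods and the dropout section; no new visits or data. SPSS offers life-table and log-rank procedures. The downsides are a second named comparison, somewhat more analysis, and coarse times, with a 6-month gap before the last visit. Recruitment began in April 2020, so the amendment should be dated and made before the groups are compared; the deciding endpoint itself does not change.
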